The efficacy of treadmill walking with partial body weight support in non-ambulatory patients after stroke is unclear. A Cochrane Collaboration Systematic Review [9] concludes that there is as yet no definitive answer about whether this intervention helps more non-ambulatory patients learn to walk compared to assisted overground walking. There are randomised controlled trials examining whether treadmill walking and partial body weight support is effective in a mixed group of ambulatory and non-ambulatory patients [7,10-13]. The only RCTs which examine non-ambulatory patients, compare treadmill training and partial body weight support with alternative interventions such as a mechanised gait trainer [14] or aggressive bracing [15] rather than current practice. This situation has led to the Cochrane Collaboration Systematic Review [9] to recommend that separate, large number, high quality studies for non-ambulatory patients be undertaken to examine the efficacy of treadmill walking with partial body weight support after stroke.

The main objective of this randomised controlled trail is to determine whether treadmill walking with partial weight support via an overhead harness is effective at establishing independent walking (i) more often, (ii) earlier and (iii) with a better quality of walking, than current physiotherapy intervention for non-ambulatory stroke patients. The study targets stroke patients who are unable to walk independently on admission to rehabilitation. It will determine the efficacy of treadmill walking with partial weight support via an overhead harness on the establishment and quality of independent walking. Furthermore, by assessing community participation six months later, it will evaluate the longer-term effect of this intervention.

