#### Proportion of participants achieving independent walking

#### Quality of independent walking

#### Community participation

Two aspects of community participation will be measured. First, mobility status will be assessed using the 6-min walk test, number of falls since discharge, a self-efficacy questionnaire about walking capability, and the Adelaide Activities Index. Second, living arrangements will be assessed by recording the type of residence and the amount of support within the residence.

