### Sample size

130 participants will be recruited. The sample size has been calculated to reliably detect a treatment effect size of a 25% increase in proportion of independent walkers with 80% power at a two-tailed significance level of 0.05. For non-ambulatory patients, it takes an average of 3 months to achieve independent walking with about 50% walking independently at six weeks [1]. We are interested in being able to detect a 25% increase, from 50% to 75%, proportion of non-ambulatory patients walking independently by six weeks. Only an effect such as this is clinically significant enough to warrant a change in the implementation of services which would involve the re-education of physiotherapists and the expense of purchasing a treadmill and overhead harness system. The smallest number of participants to detect this difference between two proportions estimated from independent samples is 65 participants per group, ie, 130 participants in total [23]. However, since the analysis of the data is survival curve analysis, there is greater power than the calculation would suggest because the effect of dropouts is minimal in this analysis. For example, in a pre-post design trial of 6 weeks intervention, if a subject dies or is lost to follow-up (ie, drops out) at 5 weeks, there is no measurement at the post-test on which to perform an analysis. In this trial, which ascertains once a week whether independent walking has been established, they would be censored at five weeks so that they no longer form part of the total sample. However, this participant's data would be available for the five weeks they participated in the trial thereby minimising the effect of their dropping out.

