### Statistical analysis

The proportion of independent walkers and the time to achieve independent walking will be compared between the two groups using the logrank test, in which those who do not achieve independent walking are censored at the time they are discharged. Survival analysis using Cox's regression will be used to compare the times in the two groups while allowing for possible confounding variables, such as other interventions received, and baseline sitting balance.

The five variables that reflect the quality of walking: speed, affected and intact step length, step width and cadence, will be compared between the two groups using Student's t-test, or Wilcoxon's rank-sum test for variables that are clearly not Normally distributed.

The four variables that reflect the mobility status: 6-min distance, number of falls since discharge, self-efficacy questionnaire about walking capability, and the Adelaide Activities Index will be compared between the two groups using Student's t-test, or Wilcoxon's rank-sum test for variables that are clearly not Normally distributed.

The two variables which reflect living arrangements: type of residence and the amount of support within the residence, will be analysed descriptively.

Descriptive data about lesion, neglect, spasticity and sensation will be used in post-hoc multiple regression analysis to examine if these factors affected walking outcome.

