## Discussion

Australia, like many other developed nations, is undergoing a major demographic shift involving significant growth in the aged population. The Australian Government has recognised that a revolution is underway at the end of the life cycle. In its National Research Priorities, the Government has recognised that it will be important to promote healthy ageing and that this endeavour will be underpinned by research. Only by establishing evidence-based interventions, such as the one outlined in this project, will the severity of many health problems be reduced. In economic terms, if non-ambulatory patients do not learn to walk after their stroke, it is likely that they will require assisted care, placing a high burden on the community. Furthermore, given that independence in walking is a major factor in the decision to discharge patients from inpatient care, earlier independent walking should result in a reduction in length of hospital stay which should result in cost saving. The Queensland Health Report "Hospital benchmarking pricing model" has estimated the cost of a day in hospital for a neurological patient at $880. In summary, this study has the potential to reduce disability following stroke by improving the outcome of walking and thereby to reduce the burden of this condition on the community. Increasing the number of people who can walk after stroke should reduce the demand for nursing home placement.

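### Living arrangements are one of two aspects of 6-month community participation, yet the plan only describes them and commits to no between-group estimate or interval

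*Protocol article*

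**What the plan says.** Three places in the protocol article belong together.

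- **Background.** After the main objective, the article adds that "by assessing community participation six months later, it will evaluate the longer-term effect of this intervention".
- **Measurement, Community participation.** This is a 6-month outcome: "Two aspects of community participation will be measured". The first is mobility status (four variables). For the second, "living arrangements will be assessed by recording the type of residence and the amount of support within the residence".
- **Statistical analysis.** The four mobility variables get a between-group test; the sentence ends with "self-efficacy questionnaire about walking capability, and the Adelaide Activities Index will be compared between the two groups using Student's t-test", or a rank-sum test where the data are clearly not Normal. The next paragraph says of the living-arrangement variables: "type of residence and the amount of support within the residence, will be analysed descriptively".

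The main objective is about walking alone, namely whether the treadmill intervention is "effective at establishing independent walking (i) more often, (ii) earlier and (iii) with a better quality of walking". Both sample-size calculations also concern walking. The Discussion adds an expectation: "Increasing the number of people who can walk after stroke should reduce the demand for nursing home placement".

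**The concern.** Evaluating the effect of a randomised intervention means contrasting the randomised groups. For one of the two named aspects of community participation the plan commits to no such contrast: no test, no estimated difference, no interval.

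This is more than detail left to a fuller document. The walking, gait-quality and mobility paragraphs of the same section all speak of comparing groups and name a method. Only the living-arrangements paragraph switches to description, so the article states a choice.

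What is at stake is modest. If the choice is carried out as group percentages alone, readers will compare them anyway, with nothing to show how far chance could explain a difference in small numbers. The data will already have been collected, so an estimate with its uncertainty would cost almost nothing.

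**Working it through.** **The plan's own figure first.** The only sample size for a proportion is 65 per group for 50% v 75%, "with 80% power at a two-tailed significance level of 0.05" (Sample size).

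- Without continuity correction: n = [1.96·√(2 × 0.625 × 0.375) + 0.8416·√(0.25 + 0.1875)]² / 0.25² = (1.3419 + 0.5567)² / 0.0625 = 57.7, so 58 per group.
- With continuity correction: (57.7/4) × [1 + √(1 + 4/(57.7 × 0.25))]² = 65.4, so 66 per group if rounded up.

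The stated 65 is reproduced to within rounding. It concerns walking at six weeks and does not bear on residence.

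**Numbers available at 6 months.** The Sample size section assumes 20% loss to follow-up when it counts participants with gait-quality data. Applied to residence (an assumption), 65 × 0.8 = 52 per group, 104 in all.

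**Precision of a difference in residential care.** The documents give no rate, so a range is assumed. For a common rate p, the 95% half-width is 1.96·√(2p(1−p)/n).

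| Assumed rate | Half-width, n = 52 per group | Half-width, n = 65 per group (no loss) |
|---|---|---|
| 10% | 11.5 points | 10.3 points |
| 20% | 15.4 | 13.8 |
| 30% | 17.6 | 15.8 |
| 40% | 18.8 | 16.8 |
| 50% | 19.2 | 17.2 |

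**What a halving would look like (assumed rates, n = 52 per group).**

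- 20% v 10%: 0.10 ± 1.96·√((0.16 + 0.09)/52) = 0.10 ± 0.136, or −3.6 to +23.6 points.
- 30% v 15%: 0.15 ± 1.96·√((0.21 + 0.1275)/52) = 0.15 ± 0.158, or −0.8 to +30.8 points.

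**Power, had a test been intended.** For 20% v 10% with 52 per group: z = (0.10 − 1.96·√(2 × 0.15 × 0.85/52)) / √((0.16 + 0.09)/52) = (0.100 − 0.137)/0.0693 = −0.54, so power is about 30%. For a 10-point reduction from 30%, 40% or 50%, power is about 22%, 19% and 17%. The reduction detectable with 80% power is about 17 points from 20%, 21 from 30%, 24 from 40% and 26 from 50%. From 10%, no reduction reaches 80%.

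An interval can therefore be given and would be informative about uncertainty, but the trial cannot test modest differences in residence with any force.

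**The case against.** The best case for the plan is that it openly pre-specifies description for two categorical outcomes on which it was not powered. That is common practice and contradicts nothing else in the article. The Background speaks of evaluating a longer-term effect; it does not promise a formal test of every component. Describing results does not strictly rule out group percentages with intervals, and a condensed article may leave such detail to a fuller document. The low power above is itself a respectable reason not to test.

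Much of this stands. It makes the point minor, and it argues for estimation over testing. It does not remove the gap between saying that community participation will show an effect and committing to no estimate of that effect for one of its two aspects. Low power is a reason to show the interval.

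Three stronger readings are tempting, and the documents do not support them.

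- *The trial claims to reduce nursing-home placement and leaves that claim untested.* The Discussion sentence is an expectation that depends on more people walking, and walking is formally compared. Residence appears in no objective or hypothesis.
- *Half of the longer-term objective goes without inference.* Living arrangements supply two of six community-participation variables, and community participation is one of three 6-month outcome headings, beside the proportion walking and the quality of walking.
- *Residence is needed because it is the outcome that keeps non-walkers in the comparison.* It does include them, but falls, self-efficacy and the Adelaide Activities Index are not restricted to walkers either, and they are already compared between groups.

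**Conclusion.** The point holds as a minor, cheap improvement to a secondary outcome. The article says community participation will be used to evaluate the longer-term effect, names living arrangements as one of its two aspects, and then commits to no between-group estimate or interval for them. It is not an error in a trial hypothesis, and no sample size, alpha or power figure changes.

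The size of the uncertainty that would go unreported is a half-width of about 11.5 to 19 points. This rests on assumed residential-care rates of 10% to 50%, on the plan's 20% loss applying to residence data as well, and on a simple large-sample interval for a difference in proportions. With no loss the range is about 10 to 17 points, so the conclusion does not depend on the loss assumption.

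**What to change.** In the Statistical analysis section, replace the sentence on living arrangements with wording such as:

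> The proportion living at home, as opposed to in residential care, at 6 months will be reported by randomised group as a risk difference with 95% confidence interval, in all participants followed, walkers and non-walkers. This is a secondary outcome, reported for estimation and not as a confirmatory test. Amount of support will be described by group.

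More elaborate analyses are not advised here. The article gives no categories or ordering for amount of support, so an ordered rank-based comparison would rest on a scale it does not define. Stratifying by site and sitting balance would spread about 104 participants over six strata, roughly 17 each or 8 to 9 per arm. At assumed rates of 10% to 20%, that is only one or two residential-care cases per arm in each stratum.

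The cost is one extra secondary comparison on data the trial already plans to collect, with an interval that will be wide and may well include no difference. If the sponsor prefers description only, the Background statement about evaluating the longer-term effect should be qualified so that it does not cover living arrangements.

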## Discussion

Australia, like many other developed nations, is undergoing a major demographic shift involving significant growth in the aged population. The Australian Government has recognised that a revolution is underway at the end of the life cycle. In its National Research Priorities, the Government has recognised that it will be important to promote healthy ageing and that this endeavour will be underpinned by research. Only by establishing evidence-based interventions, such as the one outlined in this project, will the severity of many health problems be reduced. In economic terms, if non-ambulatory patients do not learn to walk after their stroke, it is likely that they will require assisted care, placing a high burden on the community. Furthermore, given that independence in walking is a major factor in the decision to discharge patients from inpatient care, earlier independent walking should result in a reduction in length of hospital stay which should result in cost saving. The Queensland Health Report "Hospital benchmarking pricing model" has estimated the cost of a day in hospital for a neurological patient at $880. In summary, this study has the potential to reduce disability following stroke by improving the outcome of walking and thereby to reduce the burden of this condition on the community. Increasing the number of people who can walk after stroke should reduce the demand for nursing home placement.
